### Exercise prescription

Participants will be asked to self-rate their baseline activity levels as one of three categories as per American College of Sports Medicine (ACSM) guidelines:Sedentary or minimally active, not completing any moderate to vigorous activity (equivalent to poor fitness levels).Sporadic physical activity, suboptimal exercise (equivalent to fair fitness levels).Habitual physical activity, regular moderate to vigorous exercise (equivalent to average fitness levels).

Exercise intensity will be prescribed using individualised heart rate reserve (HRR) ranges in accordance with the ACSM guidelines. The following formula will be used to calculate HRR and heart rate (HR) range prescriptions: (target % × [maximum HR – resting HR] + resting HR). For each participant, age-predicted maximal HR will be calculated using the following equation: (206.9 – [0.67 × age]) [38]. Participants with self-rated ‘poor’ fitness levels (category 1) will commence the programme at an aerobic intensity of 40–50% HRR. Those with self-rated ‘fair’ fitness levels (category 2) will commence the programme at an aerobic intensity of 50–60% HRR, and those with self-rated ‘average’ fitness levels (category 3) will commence the programme at 55–65% HRR. The duration and frequency of the home exercise programme sessions is outlined in Table 2.

**Table 2 Tab2:** Home-based exercise intensity

Home-based walking programme		Exercise intensity (% heart rate reserve) by baseline fitness group			Time	
		Poor	Fair	Average	Days/week	Duration (min)
Month 1	Week 1	40–50%	50–60%	55–65%	2	20
	Week 2	40–50%	50–60%	55–65%	3	20
	Week 3	45–55%	55–65%	60–70%	3	20
	Week 4	45–55%	55–65%	60–70%	3	30
Month 2	Week 5	50–60%	60–70%	65–75%	3	30
	Week 6	50–60%	60–70%	65–75%	4	30
	Week 7	55–65%	65–75%	65–75%	4	30
	Week 8	55–65%	65–75%	65–75%	5	30
Month 3	Week 9	60–70%	65–75%	65–75%	5	30
	Week 10	60–70%	65–75%	65–75%	5	30
	Week 11	60–75%	65–75%	65–75%	5	30
	Week 12	60–75%	65–75%	65–75%	5	30
Month 4	Weeks 13–16	60–75%	65–75%	65–75%	6	30
Month 5	Weeks 17–20	60–75%	65–75%	65–75%	6	30
Month 6	Weeks 12–24	60–75%	65–75%	65–75%	6	30

Patients will also be encouraged to use the Borg Breathlessness Scale. Using this scale, participants will give a subjective rating of perceived exertion. It is a widely used and reliable indicator to monitor and guide exercise intensity [39]. The scale allows individuals to subjectively rate their level of exertion during exercise and can be used to correlate exertion levels with exercise heart rates [40]. The Borg scale will be particularly valuable with participants on beta blockers as measures of exercise intensity are inaccurate or dampened on these medications and polar monitors may not reflect an accurate heart rate during exercise.

Forms of aerobic exercise undertaken at the supervised exercise classes will specifically avoid activities which may be associated with higher risk (e.g. the use of rowing machines in participants with lumbar spinal metastases). Walking on treadmills is a low-risk exercise activity.

### Exercise follow-up

Participants will be invited to attend outpatient departments 6 months after T0 and the trial datasheet, questionnaire, and physical function measures will again be completed. Blood samples will be obtained in the same fashion as for the T0 visit. All patients will be offered a personal exercise advice session at study end to discuss long-term compliance to physical activity guidelines. Any patients demonstrating a need for further follow-up in relation to their physical activity levels will be advised to attend their GP for a referral to the GP exercise scheme. After this visit, participants will be thanked for their involvement and discharged from the study.

### Study duration

The study is scheduled to last for 4 years; initial funding was drawn down in April 2014. Enrolment commenced in November 2014 and closed in May 2017 in order to allow enrolled participants to complete their 6 months of follow-up and exercise programme and for all laboratory work and analysis to be finished before the study completion date.

### Patient withdrawal and off-study procedure

Patients are free to withdraw from participation in the study at any time upon request. An off-study form must be completed and sent to the ExPeCT research team if a patient withdraws from the study or leaves due to another reason (e.g. study completion, extraordinary medical circumstances, lost to follow-up).

### Incident reporting

The occurrence and severity of any incidents from the time of consent to completion of the programme at 6 months will be recorded by the chartered physiotherapist on a standardised reporting form (e.g. adverse events occurring as a result of exercise or adverse reactions to study blood draws). All incidents will be reported to the site PI. Incidents will be followed until resolution or until a patient withdraws from the study or leaves due to another reason (e.g. study completion, extraordinary medical circumstances, lost to follow-up). Recurrent incidents in the same patient will be counted as separate incidents.

### Data management

The ExPeCT research team will be the only people with access to the data collected in the course of this project. Data analysis will be performed at St. James’s Hospital by the in-house bioinformatics team and other members of the ExPeCT research team. At the end of the study period, when all analysis is complete, data will be retained by the ExPeCT research team. Data will be securely stored for up to 10 years with the option of requesting ethical permission for a prolonged storage time.

### Sample size

We will recruit 200 participants over the lifetime of the study, evenly divided between the exercise group and the control group. To calculate the power of the study, we used data from a previous study of ovarian cancer cell lines which showed approximately 2% platelet adhesion [21]. A standard deviation (SD) varying from 2% to 10% would enable us to detect a difference of platelet cloaking of between 0.79% and 3.9%. Research into this area is at an early stage and the clinical importance of specific incremental changes in the degree of platelet cloaking is as yet uncertain, but its elucidation is beyond the scope of this study.

With regard to the detection of changes in platelet cloaking with time, and taking the same assumptions regarding SD of platelet adhesion in PrCa CTCs as in project 1, we will be able to detect a change of 1.8% platelet cloaking between any two time points in the 100 participants in each of the exercise and the control groups, determined by paired *t* testing. A SD varying from 2% to 10% would enable us to detect a difference of platelet cloaking of between 0.56% and 2.8%. Generalised linear mixed models will be employed in order to account for the correlation between multiple measurements in the same experimental subject.

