### Metabolic syndrome and prostate cancer

Obesity, known to be associated with a pro-inflammatory, pro-thrombotic humoral milieu, confers a worse prognosis in PrCa. Between 1990 and 2002, Irish male obesity increased from 8% to 20%, with a further 47% of men overweight [3]. Metabolic syndrome (MS) is a constellation of risk factors for cardiovascular disease, with central adiposity and insulin resistance being the most important components. Male hypogonadism, due to androgen deprivation therapy (ADT)—the mainstay of treatment for locally advanced and metastatic PrCa—is an independent risk factor for the various components of MS [4–8]. MS is present in 50% of all men undergoing long-term ADT [9] and is associated with progression of PrCa [10]. This may explain the excess non-cancer mortality in this population [11].

MS is characterised by low-level chronic systemic inflammation. Increasing evidence suggests that substantial cross-talk occurs between molecular pathways involved in inflammation, coagulation, and obesity [12]. Elucidation of how these pathways interact with PrCa cells may shed light on why obesity disimproves PrCa prognosis.

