### ExPeCT study design

This international multicentre prospective study will recruit men with metastatic PrCa from five Irish hospitals and one UK hospital. This study incorporates both an observational component, with exposed and non-exposed groups defined based on body mass index (BMI), and an exercise component, with randomization to exercise and control groups for a supervised exercise programme. Participants with metastatic prostate cancer will be recruited and divided into exposed (BMI ≥ 25 kg/m^2^) and non-exposed groups (BMI < 25 kg/m^2^). All exposed and non-exposed participants will be randomised to an exercise group or a control group, helping to minimise bias. The exercise group will participate in a 6-month exercise programme, comprising a weekly group exercise class and a home-based exercise programme. Participants will also be encouraged to complete activity diaries. From baseline (T0) to 3 months (T3), participants in the exercise arm will meet in small groups with a chartered physiotherapist for 1 h per week. At these sessions, participants will be educated about using the Polar heart rate monitors, prescribed their target exercise intensity, and complete a half-hour group aerobic exercise class. From T3 to 6 months (T6) continued aerobic exercise will be encouraged but classes will not be supervised by a chartered physiotherapist. All patients will be offered a personal exercise advice session at the study end to discuss long-term compliance to physical activity guidelines. Any patients demonstrating a need for further follow-up in relation to their physical activity levels will be advised to attend their general practitioner (GP) for a referral to the GP exercise scheme.

The study design consists of four main projects (Fig. 1):

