**Fig. 1 Fig1:**
[figure not shown]
Schematic of the four projects involved in the ExPeCT trial. *BMI* body mass index, *CTC* circulating tumour cell, *H&E* haematoxylin and eosin, *NK* natural killer, *TNF* tumour necrosis factor

Project 1: CTCs will be enumerated in the T0 samples. Adherent platelets will be quantified and compared between the exposed and non-exposed groups, and correlated with clinicopathological parameters.Project 2: The exercise group will undertake a regular supervised aerobic exercise programme, whereas the control group will not. T3 and T6 blood samples will be assessed for CTC numbers and platelet cloaking. Changes will be compared with the T0 sample, and between exposed and non-exposed, and exercise and control groups. Participants will complete a detailed questionnaire to assess QoL and other parameters at each visit.Project 3: Blood samples will be assessed for NK cell number and activation, markers of systemic inflammation, adipokines, and serum factors related to platelet activation. The prostate needle core biopsies (NCBs) will be examined microscopically for atrophy and inflammation by morphology and immunohistochemistry, with particular reference to NK cells. All variables will be correlated with platelet cloaking.Project 4: NCBs will be assessed for expression of an obesity-associated lethality gene signature (whose genes are known to play a role in obesity or platelet aggregation and coagulation), and correlated with platelet cloaking of CTCs.

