### Statistical analysis

Project 1 will compare the number of cloaked platelets, comparing healthy weight and overweight men using either the *t* test or the non-parametric Mann-Whitney test, depending on the normality of the data. Linear regression models will be used to test the association between obesity and extent of platelet cloaking, adjusting for potential confounders such as age, use of medications, and smoking. If the data are not normally distributed then a log transformation will be employed. In addition to comparing overweight and healthy weight men as a binary exposure, BMI will be modelled as an ordinal variable (<18.5, 18.5–24.9, 25.0–27.4, 27.5–29.9, 30+) and as a continuous variable and to test for linear trends with the log likelihood ratio test of nested models.

Project 2 will compare measurements of platelet cloaking at baseline and months 3 and 6 follow-up time points among men randomised to the exercise and control arms, in both the exposed (BMI ≥ 25) and non-exposed (BMI < 25) groups. Intention-to-treat analyses will use linear mixed-effect models to incorporate each biomarker for a given participant over time. BMI will also be stratified to look at potential effect modification. To estimate longitudinal changes in quality of life scores from baseline, the primary analysis will be carried out using a mixed-effects model for repeated measures.

Project 3 will examine the extent of the inflammatory infiltrate in diagnostic NCBs. All variables will be correlated with CTC numbers and platelet cloaking using basic descriptive statistics such as Pearson correlation coefficients for continuous variables and simple *t* tests for categorical variables. In the event of skewed distributions or sparse data, we will use non-parametric tests such as the Spearman correlation and Mann-Whitney. Moreover, a principal component analysis will be undertaken to estimate the proportion of variability in platelet cloaking and CTC number which is explained as a function of the obesity inflammatory biomarkers. The biomarkers will be modelled as principal components in the linear regression and adjusted for potential confounders such as age, smoking, and other factors.

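### The Project 1 detectable difference of 0.79%–3.9% rests on two equal groups of 100, but Project 1 compares BMI groups, which nothing in the article makes equal

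*Protocol article*

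**What the plan says.** The Sample size section opens with the total and its division: "We will recruit 200 participants over the lifetime of the study, evenly divided between the exercise group and the control group". In the same paragraph it gives a two-group sensitivity: "A standard deviation (SD) varying from 2% to 10% would enable us to detect a difference of platelet cloaking of between 0.79% and 3.9" per cent. It names neither the groups nor alpha nor power.

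The next paragraph turns to change over time, "taking the same assumptions regarding SD of platelet adhesion in PrCa CTCs as in project 1", and gives a paired result: "A SD varying from 2% to 10% would enable us to detect a difference of platelet cloaking of between 0.56% and 2.8" per cent, for the 100 men in each arm.

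Project 1 is described under Fig. 1: "Adherent platelets will be quantified and compared between the exposed and non-exposed groups". The ExPeCT study design section defines those groups: "Participants with metastatic prostate cancer will be recruited and divided into exposed (BMI ≥ 25 kg/m^2^) and non-exposed groups (BMI < 25 kg/m^2". The Statistical analysis section gives the Project 1 test, "comparing healthy weight and overweight men using either the *t* test or the non-parametric Mann-Whitney test".

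The only prevalence figures are in the background section on metabolic syndrome: "Irish male obesity increased from 8% to 20%, with a further 47% of men overweight".

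**The concern.** A detectable difference depends on the sizes of the two groups being compared. Randomisation can make the exercise and control arms equal. It cannot make the BMI groups equal, because BMI is a characteristic the men bring to the trial. If the Project 1 range was worked out with 100 v 100, the arm sizes were used for a comparison that is not between arms.

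Project 1 tests the first of the four hypotheses, on the primary endpoint. A reader of a null Project 1 result would use the published range to judge what size of difference the study could have missed, and would credit it with more sensitivity than an uneven split gives.

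**Working it through.** **Inputs.** Total 200; SD 2% to 10%; stated range 0.79% to 3.9%; paired range 0.56% to 2.8% with 100 men per arm (all from Sample size). Alpha and power are not stated. I assume two-sided 5% and 80%, so z(0.975) + z(0.80) = 1.960 + 0.842 = 2.8016.

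**Step 1: check the assumed alpha and power on the paired range.** Detectable change = 2.8016 × SD / √100.
- SD 2%: 2.8016 × 2 / 10 = 0.560%
- SD 10%: 2.8016 × 10 / 10 = 2.80%

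Both match the article. With 90% power the same formula gives 0.648% and 3.24%, which do not.

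**Step 2: reproduce the two-group range.** Detectable difference = 2.8016 × SD × √(1/n1 + 1/n2). With 100 v 100, √(0.01 + 0.01) = 0.14142.
- SD 2%: 2.8016 × 2 × 0.14142 = 0.792%
- SD 10%: 2.8016 × 10 × 0.14142 = 3.96%

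This is the stated range, with the upper end cut to 3.9. Other standard choices at 100 v 100 do not fit: one-sided 80% gives 0.703% and 3.52%, one-sided 90% gives 0.828% and 4.14%, two-sided 90% gives 0.917% and 4.58%.

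**Step 3: how uneven could the groups be and still give 0.79%?** With n1 + n2 = 200, 1/n1 + 1/n2 = 200/(n1 × n2).
- 108 v 92: 5.6032 × √(200/9936) = 0.795 (0.79496 before rounding), which still prints as 0.79
- 109 v 91: 5.6032 × √(200/9919) = 0.796, which prints as 0.80

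So the lower figure needs equal or nearly equal groups. Because n1 × n2 is largest at 100 × 100, equal groups are also the most favourable case for 200 men.

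**Step 4: other BMI splits.** Same formula. Power at a true difference of 0.79% with SD 2% is Φ(0.79 / (2 × √(1/n1 + 1/n2)) − 1.96).

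| Share with BMI ≥ 25 | Groups | √(1/n1 + 1/n2) | SD 2% | SD 10% | Power at 0.79%, SD 2% |
|---|---|---|---|---|---|
| 50% | 100 v 100 | 0.1414 | 0.79% | 3.96% | 79.8% |
| 60% | 120 v 80 | 0.1443 | 0.81% | 4.04% | 78.1% |
| 67% | 134 v 66 | 0.1504 | 0.84% | 4.21% | 74.8% |
| 75% | 150 v 50 | 0.1633 | 0.91% | 4.57% | 67.7% |

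With the t distribution in place of the normal, power is 79.4% at 100 v 100 and 74.3% at 134 v 66.

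The 67% row comes from the background section: 20% obese + 47% overweight = 67%, and 0.67 × 200 = 134. The 60% and 75% rows are assumed shares on either side of it.

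**The case against.** **Attribution.** The sentence with the range names neither Project 1 nor BMI, and it follows the statement about the exercise and control arms. Read alone, 0.79% is correct for a comparison of two arms of 100. The later back-reference to Project 1 concerns the SD assumption and does not say which groups were compared. This shows that the link is inferred, but the link still holds: only one calculation precedes the back-reference, and the study design has Project 1 as the BMI comparison.

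**Silence.** The article contains excerpts from a full protocol that is not shown, and a BMI recruitment target could be there. That is possible. What can be said is that the article prints the figure without anything that would make the BMI groups equal.

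**The 134 v 66 split.** A reader might infer that the article's own figures split this trial's sample 134 to 66. They do not. The 67% describes Irish men in general, for a period ending in 2002, and is given as disease background; one of the six recruiting hospitals is in the UK. The Discussion calls androgen deprivation a cause of obesity, which hints at a higher share in these men, but no figure is given.

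**Size.** At 60% exposed almost nothing changes. The article's fivefold SD range is a far larger uncertainty, it concedes that the clinical importance of small changes in cloaking is not known, and Project 1 also models BMI as ordinal and continuous, where the two-group split does not govern sensitivity. All of this stands and limits the weight of the point. It does not make the published two-group figure fit the two-group comparison.

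**Rounding.** Printing 3.96 as 3.9 is trivial, and I do not press it.

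**Conclusion.** The point holds, with modest consequences. The Project 1 range takes group sizes that the article supports only for the exercise/control contrast and applies them to the BMI contrast. The error can run only one way: for 200 men, no BMI split gives a smaller detectable difference than the one implied by equal groups.

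At the illustrative 67% the detectable difference rises by about 6% (0.843 / 0.792 = 1.06) and power at the stated lower figure drops by about five points. At 75% exposed the rise is about 15% (0.915 / 0.792 = 1.155).

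This rests on three inferences: that the first calculation is the Project 1 one, that alpha and power are two-sided 5% and 80% (supported by the paired range), and that the BMI groups are not close to equal.

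A reader might go further and conclude that Project 1 is inadequately powered or that 200 men is the wrong number. The article does not support that. It sets no target difference for Project 1 and states no power that would be missed; only the stated sensitivity needs correcting.

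**What to change.** Rewrite the sentence so that it names the contrast (BMI ≥ 25 v BMI < 25 at T0), states alpha, sidedness and power, and gives the detectable difference for an assumed BMI split or a short range of splits. With two-sided 5% and 80% power that could read 0.81%–4.0% at 60% exposed, 0.84%–4.2% at 67% and 0.91%–4.6% at 75%. Any use of 134 v 66 should be labelled an assumption taken from general-population data.

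The article says enrolment closed in May 2017, so the T0 BMI counts of the enrolled men could replace the assumed split. The planning SDs of 2% to 10% should be kept, so that the figure remains a statement of design sensitivity and does not become power computed from the results. Confidence intervals will show the precision actually achieved.

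The cost is one corrected sentence and a slightly less favourable figure. Neither the sample size, the randomisation nor the analysis needs to change.

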**Fig. 2 Fig2:**
[figure not shown]
ExPeCT trial flowsheet

Upon registration of new participants, a signature confirming eligibility for the trial must be obtained from a treating physician involved in ExPeCT recruitment. Each registered patient will receive a unique participant identifier number (PIN). In order to ensure random allocation of participants to each study group, the computer programme Graphpad will be used to randomly assign a treatment group to each PIN. When issuing each PIN, two gatekeepers (1 in Ireland and 1 in the UK) will inform the research team of the treatment allocation of the participant. If a participant chooses to withdraw from the study, all data obtained up to the point of withdrawal will be carried forward unless requested otherwise.

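### The paired detectable change assumes that all 100 men recruited to each arm give evaluable samples at both visits, with no allowance for loss

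*Protocol article*

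**What the plan says.** The Sample size section of the protocol article sets recruitment: "We will recruit 200 participants over the lifetime of the study, evenly divided between the exercise group and the control group". That is 100 men per arm at randomisation.

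For change over time it gives a point figure of 1.8% for any pair of visits, by paired t test, and it names the men on whom this rests: the change is to be found "in the 100 participants in each of the exercise and the control groups". It then gives a range: an SD of 2% to 10% corresponds to a detectable change of 0.56% to 2.8%. The SD is brought over from the first calculation in the section: "taking the same assumptions regarding SD of platelet adhesion in PrCa CTCs as in project 1". The section adds that mixed models will handle repeated measurements, and the Statistical analysis section names them for the intention-to-treat analysis of Project 2.

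Two other places deal with men who leave early. Under Participant enrolment procedure (text after Fig. 2), "all data obtained up to the point of withdrawal will be carried forward unless requested otherwise". Under Patient withdrawal and off-study procedure, a form is required "if a patient withdraws from the study or leaves due to another reason", and the examples include extraordinary medical circumstances and loss to follow-up. Neither place gives an expected rate, and the Sample size section mentions no allowance.

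**The concern.** A paired t test uses only men with a value at both visits. Here the number of pairs in the calculation equals the number of men recruited to the arm, so nothing is held back for missed visits, withdrawal or samples that cannot be evaluated. The statement covers any pair among T0, T3 and T6, so it needs complete data at all three.

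The participants have M1 disease and are followed for six months, and the article sets out procedures for men who leave. If some do leave, a null result at T3 or T6 would be read against a better sensitivity than the trial had.

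**Working it through.** **Inputs from the document.** 100 pairs per arm; SD 2% to 10%; printed paired range 0.56% to 2.8%; point figure 1.8% (all from Sample size).

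**Assumed, because not stated.** Two-sided significance level 0.05 and power 80%; loss of 10%, 20% or 30% of pairs per arm.

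**Step 1: reproduce the printed range.** With the normal approximation,

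detectable change = (1.960 + 0.8416) × SD / √n = 2.8016 × SD / √n.

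- n = 100, SD 2%: 2.8016 × 2 / 10 = 0.560%
- n = 100, SD 10%: 2.8016 × 10 / 10 = 2.802%

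Both ends match. The other combinations tried do not fit: one-sided 5% with 80% power gives 0.50% and 2.49%, one-sided 5% with 90% power gives 0.59% and 2.93%, and two-sided 5% with 90% power gives 0.65% and 3.24%. The noncentral t version at two-sided 5% and 80% power gives 0.566% and 2.829%, so the approximation is adequate. The 1.8% figure corresponds to an SD of 1.8 / 0.28016 = 6.4%, which lies inside the range but is not stated.

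On these assumptions the printed range is the result for 100 complete pairs, that is, for every man recruited to the arm.

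**Step 2: allow for loss.** If a fraction d of pairs is missing, n becomes 100(1 − d) and the detectable change is multiplied by 1/√(1 − d). Power at the printed change is Φ(2.8016 × √(1 − d) − 1.960).

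| Assumed loss | Pairs per arm | Multiplier | SD 2% | The 1.8% figure | SD 10% | Power at printed change |
|---|---|---|---|---|---|---|
| 0% | 100 | 1.00 | 0.56% | 1.8% | 2.80% | 80% |
| 10% | 90 | 1.05 | 0.59% | 1.90% | 2.95% | 76% |
| 20% | 80 | 1.12 | 0.63% | 2.01% | 3.13% | 71% |
| 30% | 70 | 1.20 | 0.67% | 2.15% | 3.35% | 65% |

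**Step 3: attendance is not the only condition.** The Project 4 text in Statistical analysis grades cloaking by the proportion of CTCs that carry platelets. On that scale a sample in which no CTC is found has no value. A man who attends both visits may therefore still not supply a pair, so d should count non-evaluable samples as well as men who leave.

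**Step 4: which printed figures are touched.** The first range in the section, 0.79% to 3.9%, fits two groups of 100: 2.8016 × SD × √(2/100) = 0.79% at SD 2% and 3.96% at SD 10%. The paired paragraph's reference back to Project 1 ties that range to the comparison of BMI groups on T0 samples. Loss after T0 does not enter it.

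**The case against.** **There is no arithmetic error, and an article may leave the loss rate to the full protocol.** The first part is right: the printed figures follow from the printed inputs. The second does not dispose of the point, because the number of pairs is stated in the article and equals the number recruited.

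**A reader might infer that the plan itself predicts loss.** It does not. The withdrawal section sets out a right and a form, and its list of reasons includes ordinary study completion. The enrolment text says what happens to data already collected. These passages provide for loss without forecasting it, so every loss rate above is an assumption.

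**A reader might infer that any loss puts the printed figures out of reach.** That is too strong. If the Project 1 SD is a between-person SD, using it as the SD of the paired change implies a within-person correlation of 0.5, since SD of change = SD × √(2(1 − ρ)). A correlation of 0.55, 0.60 or 0.65 would bring back 0.56%–2.8% at 90, 80 or 70 pairs. This stands as a caution. But the article states no correlation, and its range is conditional on the SD it does state. Under that SD, loss moves the figures one way only.

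**Mixed models and retained data deal with missing visits.** Mixed models keep partial data but do not recreate a missing within-man change, and the printed figure is expressly for a paired t test. If the sentence on data up to withdrawal means only that they are kept, the pairs are still missing. If it means that the last value stands in for later ones, the imputed changes are zero and dilute the mean change. Neither reading restores 100 informative pairs.

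**The effect is small.** This stands. A factor of 1.05 to 1.20 is slight beside a fivefold SD range, and the section itself says that the clinical meaning of a given change is uncertain. The difference is that the SD uncertainty is displayed, whereas full retention is built in without comment.

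**A reader might extend the point to a between-arm comparison at follow-up.** No such range is printed. The only two-group range belongs to the baseline comparison in Project 1.

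**Conclusion.** The point holds as a minor one. The within-arm paired detectable change rests on 100 complete pairs per arm, which is every man recruited to that arm, so it is valid only with no loss and fully evaluable samples at T0, T3 and T6. The size of any shortfall cannot be fixed from the document. At an assumed 10% to 30% loss the detectable change rises by about 5% to 20%, and power at the printed change falls from 80% to between about 76% and 65%. These figures rest on two-sided 5% and 80% power, inferred because they reproduce the printed range, and on the stated SD being the SD of the paired change. Nothing here calls the design, the recruitment target or the Project 1 baseline figure into question.

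**What to change.** Keep 200 men. In the Sample size section, state the assumed loss, counting non-evaluable samples, and give the paired detectable changes involving T3 and T6 for the number of men per arm expected to have evaluable samples at both visits. Restate the 1.8% figure on the same basis. As an illustration, 80 pairs per arm would give 0.63% to 3.13%, with about 2.0% in place of 1.8%. Say that the Project 1 baseline range is not subject to follow-up loss.

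The cost is a change of wording and a slightly less favourable stated sensitivity. No extra men are needed. The Study duration section says that enrolment closed in May 2017, so restating the figure is also the practical remedy.
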